### 14.4 Demographic and baseline disease characteristics

Demographic and baseline data will be summarized for each treatment group. The date of birth, gender and race of the infant will be recorded. Gestation, multiplicity, birth weight and resuscitation at delivery, including Apgar scores, will be documented. Maternal age will be recorded. We will also record administration of antenatal steroids, preterm premature rupture of membranes (evidence of and duration of), intra-partum antibiotic use, the mode of delivery and indication for mode of delivery.

#### **Descriptive analysis**

The following summary statistics will be presented to summarize demographic and baseline disease characteristics by treatment arm:

- quantitative variables will be summarized by: number of observed and missing values, mean, median, standard deviation, IQR, minimum and maximum;
- categorical variables will be summarized by: number of observed and missing values, frequencies per category, percentages per category

### 14.5 Efficacy analysis

Analysis of efficacy endpoints will be carried-out following the Intention-To-Treat (ITT) principle. A Per Protocol analysis will also be carried out on the primary endpoint for sensitivity analysis. For all statistical analysis, a p-value < 0.05 will be considered statistically significant.

Interim analysis of the primary endpoint and the important secondary endpoint, death before hospital discharge, will be performed by an external data safety monitoring board. This will be performed once half the planned sample (126 participants) have completed the trial.

#### 14.5.1 Primary efficacy endpoint

For the primary endpoint, the incidence of endotracheal intubation for respiratory failure within 120 hours of birth, the following analysis will be carried out.

- Descriptive statistics will be calculated to compare the rate of endotracheal intubation across treatment arms. Ratios of relative risk will be presented with 95% confidence intervals.
- A superiority hypothesis test (two-sided, two-proportion Z test) will be carried out to investigate whether the rate of endotracheal intubation differs between intervention and standard-of-care. In this analysis, infants intubated for signs of respiratory failure (whether or not they strictly met the pre-defined criteria in the protocol) will be considered to have met the primary endpoint.
- A competing risks model will be applied to investigate the effect of the intervention on the primary endpoint, adjusting for other outcomes that may impact on observation of the primary endpoint (e.g. death occurring before 120 hours of birth or intubation prior to 120 hours without meeting the criteria for respiratory failure defined in the protocol).
- Regression modelling will assess the effect of the intervention on the occurrence of endotracheal intubation within 120 hours of birth, adjusting for measured covariates of interest, including centre, gestational age, birth weight, gender, mode of delivery (vaginal versus caesarean birth) and antenatal corticosteroid treatment, to determine whether the estimated intervention effect is sensitive to these covariates.

#### 14.5.2 Secondary efficacy endpoints

Each categorical secondary endpoint will be analysed with the following approach.

- Descriptive statistics will be calculated to compare the rate of occurrence of the endpoint across treatment groups (frequency, percentage). Ratios of relative risk will be presented with 95% confidence intervals.
- A superiority hypothesis test (two-sided, two-proportion Z test) will be carried out to investigate whether the rate of occurrence of the endpoint differs between intervention and standard-of-care.

For the important secondary endpoint of death before hospital discharge, regression analysis will be employed to determine sensitivity of the estimated intervention effect to potentially relevant covariates; including centre, gestational age, birth weight, gender, mode of delivery (vaginal versus caesarean birth) and antenatal corticosteroid treatment.

Each quantitative secondary endpoint (e.g. duration of mechanical ventilation, duration of hospitalisation), will be analysed using the following approach.

- Descriptive statistics will be calculated to compare the endpoint across treatment groups (mean, median, standard deviation, IQR, min, max). The difference in means (or medians where relevant) between treatment groups will be presented with a 95% confidence interval.
- A superiority hypothesis test (two-sided independent sample t-test) will be carried out to test for a difference in means between control and intervention. Alternatively, if t-test assumptions are not valid, a Mann-Whitney U test will be carried out to test for a difference in the endpoint between control and intervention.

#### 14.5.3 Subgroup analysis

Subgroups of interest include infants of different gestational age strata (e.g. less than 26 weeks, and 26-28 weeks gestation at birth), and infants from different participating centres. Subgroup analysis of the primary outcome and the important secondary outcome of death before hospital discharge will be carried out for these subgroups by:

- Summarizing the frequency and rate of the outcome by treatment arm, for each subgroup separately
- Regression modelling of the outcome evaluating interaction effects for treatment type and centre, and for treatment type and gestational age

#### **14.6 Safety analysis**

Adverse events following administration of oropharyngeal surfactant will be documented e.g. bradycardia, desaturation. Should an infant require endotracheal intubation for respiratory failure, the intubation difficulty and attempts after oropharyngeal administration of surfactant will also be recorded.

Safety analyses will be carried out on patients in the Safety Set, the definition of which will be finalized in the Statistical Analysis Plan (SAP).

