### Secondary outcomes

- Intubation in the delivery room (DR)
- Number of attempts taken to successfully intubate in the DR
- Chest compressions in the DR
- Adrenaline administration in the DR
- Rectal temperature on admission to the NICU
- NICU intubation
- Surfactant use before death or hospital discharge
  - Number of doses, including total dose
  - Intra-tracheal surfactant received post-intervention
  - Doses of post-intervention surfactant
- Respiratory distress syndrome
  - Clinical evidence of respiratory distress with radiological evidence (ground glass appearance on CXR)
- Incidence of pneumothorax
  - Incidence of pneumothorax on CXR
- Incidence of pulmonary haemorrhage
  - Clinical evidence of pulmonary haemorrhage
- Mechanical ventilation
- Days of mechanical ventilation
- Use of postnatal corticosteroids for ventilator dependence
- Days of duration of respiratory support (endotracheal ventilation, high-frequency oscillatory ventilation, CPAP, heated humidified high-flow nasal cannula  $O_2$ , low flow nasal cannula  $O_2$ )
- Bronchopulmonary dysplasia (BPD) – supplemental  $O_2$  at 28 days of life
- Chronic lung disease of prematurity (CLD) – need for supplemental  $O_2$  at 36 weeks corrected gestational age (CGA) determined by physiological oxygen reduction test
- Medical treatment for a patent ductus arteriosus
  - Administration of ibuprofen or paracetamol for PDA

- Surgical treatment for a patent ductus arteriosus
- Proven necrotising enterocolitis ( $\geq$  Bell's stage 2)
- Incidence of Intraventricular haemorrhage (IVH) (any and severe: IVH grade  $\geq 3$ )
  - Evidence on surveillance cranial ultrasounds performed regularly in NICU as standard of care
- Incidence of cystic periventricular leukomalacia
  - Evidence on surveillance cranial ultrasounds performed regularly in NICU as standard of care
- Retinopathy of prematurity treated with laser photocoagulation or intravitreal injections
  - Evidence on surveillance ophthalmology review performed regularly in NICU as standard of care
- Death before hospital discharge
- Survival without BPD at hospital discharge
- Survival without CLD at hospital discharge
- Duration of hospitalisation
- Use of home oxygen therapy
  - Discharged home on oxygen therapy

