##### Safety Assessment

The following safety evaluations will be performed during the study: adverse event monitoring. Surfactant has an excellent safety profile for use. Previously reported adverse effects include bradycardia and desaturation.

We will also record the number of intubation attempts in DR post oropharyngeal surfactant use.

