1. Bradycardia, hypotension, hyperoxia, cyanosis, apnoea, oxygen desaturations  
These events frequently occur several times per day in this population, whether or not they have received surfactant. Most often these events are short in duration and not of clinical significance. Regular reporting of these adverse events in the CRF is not required.
2. Intracranial haemorrhage  
Some degree of intracranial haemorrhage is detected in  $\geq 30\%$  of infants in this population, whether or not they have received surfactant. Regular reporting of these adverse events in the CRF is not required. All enrolled infants are being screened for intracranial haemorrhage; it is being recorded in the CRF and measured as a secondary outcome.
3. Bronchopulmonary dysplasia  
Bronchopulmonary dysplasia occurs in up to  $\geq 50\%$  in this population of infants, whether or not they have received surfactant. Regular reporting of these adverse events in the CRF is not required. All enrolled infants are being screened for bronchopulmonary dysplasia; it is being recorded in the CRF and measured as a secondary outcome.
4. Pneumothorax, pulmonary haemorrhage  
These are rare events in this population of infants, whether or not they have received surfactant. Regular reporting of these adverse events in the CRF is not required. All enrolled infants are being screened for pneumothorax and pulmonary haemorrhage; it is being recorded in the CRF and measured as a secondary outcome.
5. Endotracheal intubation complication  
Endotracheal intubation complication is not relevant as we are not giving surfactant via this route of administration as the intervention arm for this study. Regular reporting of these adverse events in the CRF is not required.

Only AEs which are not directly associated to the underlying condition of extreme prematurity should be reported. The following information will be recorded: description, date of onset and end date, severity, assessment of relatedness to the study medication, other suspect medication or device and action taken. Follow-up information should be provided as necessary.

AEs considered related to the study medication as judged by an investigator or the sponsor will be followed until resolution or until the event is considered stable. All related AEs that result in a subject's withdrawal from the study or are present at the end of the study, should be followed up until a satisfactory resolution occurs.

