##### **Adverse events**

The number of adverse events (i.e. all events occurring, worsening or becoming serious after the randomisation), and the number and percentage of infants reported as having at least one emergent adverse event, will be reported by system organ class and preferred term, for each treatment group.

The same description will be performed for serious adverse events (SAE), severe AE, AE treatment related and AE leading to IMP withdrawal.

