##### 3.2.3 Safety population

Patients in the intervention arm who received prophylactic surfactant and all patients in the control arm (for comparison)

|         |                                           |               |
|---------|-------------------------------------------|---------------|
| UCD CRC | SAP for the POPART trial                  |               |
| UCD CRC | Template: Statistical Analysis Plan (SAP) | Version: 1.0  |
|         |                                           | Page 10 of 19 |

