#### Secondary endpoints analysis

Mortality is an intercurrent event that could potentially occur before observation of many of the secondary endpoints in this trial in addition to the primary endpoint. Most secondary outcomes will involve evaluation of the intervention effect to be expected in infants while alive. Analysis of secondary endpoints will be performed on the intention-to-treat set of all randomised infants. The exceptions to this are

- Number of attempts taken to successfully intubate in the delivery room – will only be assessed for those who need to be intubated in the delivery room (intubation in the delivery room is indicated by variable **dr\_infant\_intub.factor**)
- Rectal temperature on admission to NICU as well as NICU intubation will only be evaluated for infants who are admitted to NICU alive (identified by derived variable **nicu\_admission**)

|         |                                           |              |               |
|---------|-------------------------------------------|--------------|---------------|
| UCD CRC | SAP for the POPART trial                  |              |               |
| UCD CRC | Template: Statistical Analysis Plan (SAP) | Version: 1.0 |               |
|         |                                           |              | Page 13 of 19 |

- Bronchopulmonary dysplasia (BPD) – supplemental O2 at 28 days of life - will only be evaluated for infants who are alive at 28 days of life (infants alive at 28 days to be determined by the variable **bpd\_d28.factor** )
- Chronic lung disease of prematurity (CLD), the need for supplemental O2 at 36 weeks corrected gestational age (CGA) determined by physiological oxygen reduction test - will only be evaluated for infants who are alive at 36 weeks CGA (determined by the variable **cld\_36wks.factor** )
- Duration of hospitalisation will be summarized and analyzed both for infants who survive to hospital discharge and for the whole sample. A similar approach will be used for days of mechanical ventilation and days of respiratory support.

Each categorical secondary endpoint will be analysed using the same approach as the main analysis of the primary endpoint.

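### Section 14.6 ties the recording of bradycardia, desaturation and intubation difficulty to the surfactant bolus, section 13.3 waives routine reporting of them, and controls have no matching window or form

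*Combined protocol and SAP*

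**What the plan says.** **Recording tied to the bolus.** Protocol section 14.6 says that "Adverse events following administration of oropharyngeal surfactant will be documented e.g. bradycardia, desaturation". For an infant who goes on to be intubated for respiratory failure, it adds that "the intubation difficulty and attempts after oropharyngeal administration of surfactant will also be recorded". The Safety Assessment text in section 11.3.2 uses the same trigger for the delivery room (DR): "We will also record the number of intubation attempts in DR post oropharyngeal surfactant use". Under section 11.1, controls have nothing injected into the oropharynx.

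**The waiver.** Section 13 makes adverse event (AE) collection subject to section 13.3. The first numbered item there covers bradycardia and oxygen desaturation, among others, and the fifth covers endotracheal intubation complications. Of each it says: "Regular reporting of these adverse events in the CRF is not required". The waiver has no arm restriction.

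**The comparison.** Section 14.6 counts AEs from randomisation, and these "will be reported by system organ class and preferred term, for each treatment group". SAP section 3.2.3 keeps "all patients in the control arm (for comparison"). SAP section 5.4 describes by arm any non-serious AE above 5% in either arm.

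**What both arms already have.** Section 10.3 lists "Number of attempts taken to successfully intubate in the DR" as a secondary outcome without arm restriction. SAP section 5.1.1 says that it "will only be assessed for those who need to be intubated in the delivery room", which restricts by intubation and not by arm.

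**The concern.** The acute safety question is whether a bolus into the oropharynx at birth causes bradycardia, desaturation or a harder intubation. Answering it needs the same observation in both arms over the same minutes of life. Section 13.3 itself says that bradycardia and desaturation often occur several times a day in these infants, with or without surfactant. A count from dosed infants alone therefore has no meaning without the background rate.

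Section 14.6 asks for these events after an exposure that controls never have, and section 13.3 tells sites that they need not report them. Caregivers know the allocation, so the people who give the bolus also decide what to write down. If the two sections are applied differently by arm, the safety table and the Data Safety Monitoring Board's six-monthly review would carry a difference that reflects recording and not harm.

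**Working it through.** **1. Recording routes for each observation**

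| Observation | Dosed infants | Controls |
|---|---|---|
| Transient bradycardia, desaturation | Requested by 14.6; waived by 13.3 item 1 | Waived by 13.3 item 1; no other rule |
| Intubation difficulty | Requested by 14.6; complications waived by 13.3 item 5 | Complications waived by 13.3 item 5; no other rule |
| Attempts outside the DR | Requested by 14.6 | No rule |
| Attempts in the DR | Secondary outcome | Secondary outcome |
| DR intubation, chest compressions, adrenaline | Secondary outcomes | Secondary outcomes |

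The gap is the first three rows.

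**2. Whether another provision fills it**

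- Section 11.3.4 lists an AE assessment on the day of birth for all infants, and section 14.6 counts AEs from randomisation. Collection still runs through section 13.3, which waives these events.
- For intracranial haemorrhage, bronchopulmonary dysplasia, pneumothorax and pulmonary haemorrhage, section 13.3 pairs the waiver with a secondary outcome in both arms. It does not do so for bradycardia or desaturation, and neither is among the secondary outcomes in section 10.3.
- Vital signs in section 11.3.1 cover both arms. They include pulse but not oxygen saturation, and no timing within the first minutes is given.

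**3. What each way of following the text produces**

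- Section 13.3 followed for every infant: no routine record in either arm, and no figure.
- Section 14.6 followed for dosed infants and section 13.3 for controls: a surfactant-arm figure with no usable control rate.
- The same recording in both arms by local choice: a fair comparison, which the text does not require.

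**4. Size**

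The documents give no delivery-room rate and no figure for the safety comparison, so there is no safety calculation to reproduce. The only input taken from the plan is 250 infants allocated 1:1, about 125 per arm.

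Let r be the true rate, equal in both arms, and let c_S and c_C be the proportions of events captured with surfactant and in controls.

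Spurious risk difference = r × (c_S − c_C)

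With assumed capture of 90% and 50%:

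- r = 10%: 0.10 × 0.40 = 4 points (expected 11.3 v 6.2 of 125)
- r = 30%: 0.30 × 0.40 = 12 points (33.8 v 18.8)
- r = 50%: 0.50 × 0.40 = 20 points (56.2 v 31.2)

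With equal capture the expected difference is 0 at every rate. With capture of 100% and 0% the difference equals r. All of these rates and capture proportions are assumptions.

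**The case against.** The strongest reply is that section 14.6 does not say that controls go unrecorded. AEs are counted from randomisation in both groups, an AE assessment is scheduled for every infant on the day of birth, and the monitoring board reviews both arms. The acute events that matter most clinically are randomised comparisons already: DR intubation (persistent bradycardia is one trigger for it), attempts in the DR, chest compressions and adrenaline. Apgar scores are also recorded. The CRF is not among the documents, so a page completed for both arms cannot be ruled out.

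Much of this stands, and it limits the point to the three gaps in the table. It does not close them, because general AE collection leads back to the waiver.

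A reader might also infer that the safety table must show an excess with surfactant by construction. The documents do not support that. It would require section 14.6 to be applied to dosed infants and section 13.3 to controls, and the text nowhere says so. Under-recording in both arms fits the text equally well.

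Nor should p-values be attached to such an excess. The plan specifies numbers and percentages for AEs, not tests, and the p-values would rest on assumed rates and total one-sided capture. They also depend on the test: a table of 5 v 0 of 125 gives p = 0.024 by the two-proportion Z test but about 0.06 by Fisher's exact test.

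**Conclusion.** The concern holds as an unresolved conflict between sections 13.3 and 14.6, together with the lack of a common window, definition or form for controls. It covers transient bradycardia and desaturation, intubation difficulty, and attempts outside the DR. It does not cover DR attempts. The consequence is either a risk of unequal ascertainment in an open-label trial or an acute-safety figure with no control rate.

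The size cannot be derived from the documents. The 4 to 20 points shown rest on assumed true rates of 10% to 50% and assumed capture of 90% v 50%, and the bias is zero if capture is equal. The primary endpoint, the sample size and the error rates are unaffected. This is a cheap improvement worth making, because the route is off-label and its immediate effects are what the safety comparison should address.

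**What to change.** **Protocol.** Reconcile sections 11.3.2 (Safety Assessment), 13.3 and 14.6, including its Adverse events paragraph. State that two sets of items are recorded in both arms, with the same definitions and on the same CRF page:

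- bradycardia and desaturation over one common window from birth;
- difficulty and number of attempts for any intubation for respiratory failure, in the DR or the NICU.

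Make this an explicit exception to the section 13.3 waiver. If the waiver is left untouched, the conflict remains.

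**SAP section 5.4.** Report these items by arm in the planned safety population, with risk differences and 95% confidence intervals. Difficulty and attempts exist only for infants who were intubated, a group formed after randomisation, so show the denominators and read that comparison with caution.

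**If comparable control data were not collected.** The SAP is dated April 2022, and protocol version 2.1 of November 2020 says that close-out had begun at some sites, so new recording may no longer be possible. In that case, state in SAP section 5.4 that the surfactant-arm events are reported descriptively, with no between-arm comparison.

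**Cost.** One CRF page and matching wording, with a few minutes of extra recording per control infant. The fallback costs one sentence in the SAP.

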##### **Adverse events**

The number of adverse events (i.e. all events occurring, worsening or becoming serious after the randomisation), and the number and percentage of infants reported as having at least one emergent adverse event, will be reported by system organ class and preferred term, for each treatment group.

The same description will be performed for serious adverse events (SAE), severe AE, AE treatment related and AE leading to IMP withdrawal.

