**Figure 1: Study Schema**

[figure not shown]

Prior to delivery a member of the research team or other senior doctor will approach parent(s)/guardian(s) of eligible infants to inform them about the study. Randomisation will occur at delivery. Infants will then be monitored for the duration of their hospitalisation, looking at a large number of secondary outcomes. Subjects' participation will be from time of birth until discharge from hospital.

Infants in the treatment arm will receive oropharyngeal surfactant immediately after birth and then be stabilised on CPAP. Infants in the control arm will be stabilised on CPAP immediately after delivery. Infants will then receive standard care, regardless of their group assignment. Enrolled infants will be intubated for persistent apnoea and/or bradycardia in the DR, or for respiratory failure in the NICU as specified in the protocol. Should infants in either group meet the criteria for respiratory failure following initial randomisation, they will be intubated and surfactant will be administered for treatment of RDS, irrespective of group assignment (i.e. whether or not they have previously received oropharyngeal surfactant). Further surfactant administration and all other aspects of neonatal intensive care will be at the discretion of the treating physicians.

All babies in both groups will be closely watched to see if they need extra treatment for their RDS at any stage, including surfactant given endotracheally. The babies will be treated equally and given whatever treatment is necessary, whether or not they have already been given surfactant into the oropharynx.

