#### 11.3.5 Subsequent study visits and procedures

The intervention in this study is a once-off administration of surfactant at birth. After this intervention, all other cares will be the same between infants in both arms.

Assessment of the incidence of intubation for respiratory failure is the goal and will be conducted at 120 hours post birth (visit 3).

Assessment of bronchopulmonary dysplasia will be at day 28 of life and assessment of chronic lung disease prematurity will be at CGA 36 weeks.

During hospitalisation, at all visits after and including baseline visit, the following assessments/procedures will occur:

- assess efficacy outcome measures
- assess safety (adverse event monitoring)
- dispense study medications
- record concomitant medications
- assess compliance with study medications

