#### 11.3.6 Method of assigning Subjects to treatment groups

Infants will be randomised to receive oropharyngeal surfactant or CPAP (which is the standard of care) in a 1:1 ratio using variable block randomisation, with block sizes of 4, 6 and 8. Randomisation will be stratified by participating centre. The more prematurely an infant is born, the higher their risk is of being

intubated for respiratory support in the first 120 hours of life (primary outcome). It is important to ensure balance in the risk of reaching the primary outcome between the two treatment arms at study entry; thus we will also stratify the randomisation by gestational age (<26 weeks and 26-28 weeks inclusive).

Infants of multiple gestations will be randomised as individuals.

A computer-generated randomisation schedule will be prepared by an independent statistician who will not be involved with subsequent data analysis or interpretation. The schedule will be stored securely on a password protected computer. The randomization list will be numbered using sequential 6-digit randomization codes (e.g. NMH001, NMH001,...). Each group assignment – “OROPHARYNGEAL SURFACTANT” or “CONTROL” – will be written on a card that will be labelled with its corresponding 6-digit randomisation code (e.g. NMH001). Each card will be folded in half and placed in an opaque sealed envelope that will be labelled with the same 6-digit randomisation code. The envelopes will then be placed in sequential order (e.g. NMH001, NMH002, NMH003...) in separate boxes for the two gestational age strata for each centre. At each centre, the boxes containing the envelopes will be stored securely in the neonatal intensive care unit (NICU), as the clinical team will need to have access to the randomisation envelopes. An envelope from the appropriate box (<26 weeks or 26–28 weeks) will be opened immediately before birth.

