## 13 SAFETY REPORTING

Adverse events (AEs) will be recorded throughout the study and will be evaluated and classed according to the definitions below (European Directive 2001/20/EC). All adverse events will be collected and recorded in accordance with the detailed guidance on the collection, verification and presentation of adverse event/reaction reports arising from clinical trials on medicinal products for human use ('CT-3') while referencing the protocol specific guidance included in Section 13.3.

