#### 5.4 Safety evaluation

Adverse events will be summarized for each site and for the whole sample, including:

- Total number of adverse events
  - Number and percentage of adverse events that were serious (SAES)
  - Number and percentage of adverse events that were mild, moderate and severe
  - Number and percentage of treatment-related adverse events
  - Number and percentage of adverse events that were resolved without sequelae, resolved with sequelae, ongoing, or resulted in death.
- Number of deaths (all causes) per treatment arm
- Number of deaths resulting from adverse events per treatment arm
- Number and percentage of subjects experiencing
  - Any adverse event
  - Any serious adverse event
  - Mild, moderate and severe adverse events
  - Treatment-related adverse events

Further, any non-serious adverse event occurring with a greater than 5% frequency in either treatment arm, will be described by treatment arm, including:

- System organ class
- Event term
- Number of subjects per treatment arm affected by the event
- Total number of events of this type that occurred per treatment arm

For all serious adverse events (SAEs), the above information will be reported as well as:

- Number of these SAEs causally related to treatment, per treatment arm
- Number of these SAEs with fatal outcome, per treatment arm
- Number of treatment-related SAEs of this type with fatal outcome

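### Adverse events are tabulated only from randomisation to discharge, with no early-onset table, although the drug is one dose within 5 minutes of birth

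*Combined protocol and SAP*

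**What the plan says.** **Exposure.** Protocol 11.3.5: "The intervention in this study is a once-off administration of surfactant at birth". Protocol 11.1 requires the dose within 5 minutes of birth, and under protocol 11.3.6 the randomisation envelope "will be opened immediately before birth".

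**Counting period.** Protocol 13: "Adverse events (AEs) will be recorded throughout the study". Protocol 11.1: "Subjects' participation will be from time of birth until discharge from hospital". Protocol 14.6 starts the count at randomisation: "The number of adverse events (i.e. all events occurring, worsening or becoming serious after the randomisation". It sets no earlier end point than the end of participation. These tables are by system organ class and preferred term, for each arm, and are repeated for serious, severe and treatment-related events.

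**SAP 5.4.** The summary opens with "Total number of adverse events", by site and for the whole sample, and goes on to infants with any adverse event or any serious adverse event. Nothing in it refers to time of onset.

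**What is collected.** For a reported event, protocol 13.3 asks for "description, date of onset and end date, severity, assessment of relatedness to the study medication". The schedule of events (protocol Figure 2) has an adverse event assessment at Visit 3, 120 hours after birth.

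**What is not reported.** Protocol 13.3 restricts reporting to events not directly associated with extreme prematurity. Its examples of exempt events include bradycardia, hypotension, apnoea, desaturation, intracranial haemorrhage, bronchopulmonary dysplasia, pneumothorax and pulmonary haemorrhage. Protocol 14.6, however, gives bradycardia and desaturation as examples of events after the dose that will be documented.

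**The concern.** A single bolus at birth is most likely to cause harm in the first hours or days. Infants born before 29 weeks then remain in hospital, and under observation for adverse events, until discharge. Each later event unrelated to the drug adds to both arms alike, so the relative difference shrinks and the sampling noise grows.

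A report of no excess of adverse events over the whole stay could then be read as reassurance about the period just after the dose, which no adverse event table isolates. This matters because the oropharyngeal route is unlicensed (protocol 9.2 and section 18). The plan already collects what a basic early table needs for reported events.

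**Working it through.** **The plan's own figures.** The documents give no adverse event rate, power or window, so there is no safety figure to reproduce. The arm size comes from protocol 14.2. For 46% v 28%, two-sided 5%, 80% power and mean proportion 0.37:

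n per arm = [1.96 × √(2 × 0.37 × 0.63) + 0.8416 × √(0.46 × 0.54 + 0.28 × 0.72)]² / 0.18² = (1.338 + 0.565)² / 0.0324 ≈ 112, or 224 in total, as stated.

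Then 224 / 0.90 = 249, against the stated 250. With 1:1 allocation this is 125 per arm.

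**Illustration.** Let e be an infant's risk of a reported event with early onset, and l the risk of a later event, independent and equal in both arms. Then

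whole-stay risk = 1 − (1 − e)(1 − l), and whole-stay risk difference = (e₁ − e₀)(1 − l).

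Assumptions, not document figures: e₀ = 2% (control), with e₁ = 8% or 10% (surfactant); l from 1% to 60%. Example at l = 5%: control 1 − 0.98 × 0.95 = 6.9%; surfactant 1 − 0.92 × 0.95 = 12.6%.

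Power is the exact binomial power of the pooled two-proportion Z test, two-sided 5%, 125 per arm.

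| Later events (l) | Any event, 2% v 8% early | Power, 2% v 8% | Power, 2% v 10% |
|---|---|---|---|
| Early window only | 2.0% v 8.0% | 60% | 80% |
| 1% | 3.0% v 8.9% | 52% | 72% |
| 2% | 4.0% v 9.8% | 45% | 65% |
| 5% | 6.9% v 12.6% | 33% | 50% |
| 10% | 11.8% v 17.2% | 22% | 35% |
| 20% | 21.6% v 26.4% | 14% | 21% |
| 40% | 41.2% v 44.8% | 9% | 12% |
| 60% | 60.8% v 63.2% | 7% | 8% |

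**Reading.** The direction is the same throughout: counting to discharge always loses information about an early effect. The loss runs from small (60% to 52%) to nearly complete (60% to 7%), depending on l. Protocol 13.3 pushes l down by exempting many late complications, but by how much cannot be found in the documents. No test of any adverse event is planned, so power here only measures how visible an early difference would be.

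**The case against.** A reader might infer that an acute excess would be swamped by months of unrelated events, so that the safety comparison has little chance of showing real acute harm. The documents do not support that, for four reasons.

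- **The reporting filter.** Protocol 13.3 exempts many common prematurity events, and protocol 13.4 limits serious adverse events to deaths and important medical events. Late reported events may be few, and then the dilution is modest.
- **Tables by term.** Protocol 14.6 tabulates by preferred term and arm, so within a term only later events of the same kind dilute. This stands in part: SAP 5.4 describes non-serious events by term only above 5% frequency in either arm, so a rarer acute event could sit only in the pooled totals if the SAP is followed.
- **Other acute outcomes.** Delivery-room intubation, intubation attempts, chest compressions, adrenaline and NICU admission temperature are compared by arm. The primary endpoint covers 120 hours. Deaths have Kaplan-Meier curves and Cox regression (SAP 5.1.1). This stands, but for adverse events between the delivery room and 120 hours there is no time-bound table.
- **Missing rather than diluted.** If the exemption in protocol 13.3 governs, bradycardia and desaturation after the bolus may never reach the adverse event tables, and no split by onset would recover them. This stands, and it is why the two sections have to be reconciled.

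The recorded onset is also described as a date, not a time, so a cut at exactly 120 hours may not be possible.

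**Conclusion.** The point holds in a limited form. The safety tables cover the whole stay for a drug given once at birth, and leave unused the onset dates and the 120-hour assessment that the protocol provides for. This weakens the comparison in the early period, but by an amount that the documents do not fix.

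Under the assumed 2% v 8%, visibility falls from 60% to anything between 52% and 7% for late rates of 1% to 60%. These figures rest on assumed rates, on independence of early and late events, and on the any-event total, which is the most diluted summary. They illustrate the mechanism and do not estimate this trial's loss. The early table is still worth adding, because it costs little and answers the question that the exposure raises.

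**What to change.** 1. In SAP 5.4, add a descriptive table by arm, counted per infant with 95% confidence intervals, of adverse events and serious adverse events with onset from the day of birth (day 0) to day 5. This matches the primary-endpoint window to the nearest day: it always contains the first 120 hours and may run up to about 24 hours beyond. Use the same window in both arms.
2. Keep the whole-stay tables. No extra table is needed for deaths, whose timing the Kaplan-Meier curves already show.
3. Reconcile protocol 13.3 with protocol 14.6 on whether bradycardia and desaturation after the dose are recorded, and state in the report which early events the table can and cannot contain.

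**Cost.** SAP wording and one table shell, using onset dates already specified for reported events. The counts will be small, so the table should be read through its confidence intervals rather than tests, and the cut is by day rather than by hour.
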